It is hypothesized that the exercise bouts will improve glycemic control compared with CON but that no differential effect of the exercise bouts on glycemic control will be seen.

EXPERIMENTAL DESIGN

*Sample Size:* Based on our previous study examining glycemic control after acute IW(-3) compared to CON in type 2 diabetic subjects (standardized effect size = 0.95, (21)), power calculations were performed using G*Power (v3.1.9.2, Düsseldorf, Germany). To account for multiplicity, α was set at 0.017 (0.05 / 3), and 1-β was set at 0.80. These analyses indicated that at least 12 subjects should complete the study. If a subject does not complete the study, he or she will be replaced by another subject, but the total number of subjects included will not exceed 24.

*Recruitment, information and informed consent:* Potential subjects are recruited through direct contact, advertising on "www.forsøgsperson.dk" and advertising in local newspapers. Potential subjects contact one of the project participants by telephone and are orally informed about the study. If no exclusion criteria are identified in the phone, an information meeting date is arranged, and the potential subject is informed about the possibility of inviting a private counselor to the information meeting. At least three days prior to the information meeting, written project information including consent form will be sent to the potential subject and he/she will be encouraged to read the information thoroughly.

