At the information day, extensive oral information about the scientific study will be given by one of the scientific participants. The information will be given in a closed room where only the scientific participant, the potential subject and the potential private counselor will be present. After the oral information has been given, the potential subject will be asked if he/she wants time to consider before he/she is ready to decide whether or not to participate in the study. If the potential subject does not want time to consider potential participation but is ready to decide and wants to participate in the study, the informed consent form will be signed and the screening will commence. If the potential subject wants additional time to consider whether or not to participate in the study, an agreement about a telephone meeting after approx. one week is made. The subject will be informed of the possibility of contacting one of the scientific participants by telephone, in case of questions. If the potential subject wants to participate in the study, a screening will be arranged and the signed consent form will be brought to the screening by the subject.

*Subjects and screening:* A total of n=12 type 2 diabetes patients will initially be included in the study. A medical examination, medical history, blood chemistry screen, ECG, oral glucose tolerance test (OGTT), Dual x-ray absorptiometry (DXA) scan and a physical fitness test (VO2max test) will be performed. If an individual meets the inclusion criteria, informed oral and written consent will be obtained prior to participation in the study, in accordance with guidelines developed by the ethical committees.

*Inclusion Criteria:*

- Type 2 diabetes mellitus
- Age >30 y
- BMI >18 but <40 kg/m2
- Agreement to pause non-insulin anti-diabetic medication from 2 days before to the end of each intervention

*Exclusion Criteria:*

- Pregnancy
- Smoking
- Contraindication to increased levels of physical activity (22)
- Insulin dependence
- Evidence of thyroid, liver, lung, heart or kidney disease

STUDY DESIGN

Subjects will be instructed to ingest the same food at each day preceding the interventions, to avoid alcohol and caffeine for 24 hours prior to the interventions and to abstain from vigorous physical activity for 48 hours prior to the interventions.

*Interventions:* The 3 interventions will be performed in counter-balanced order and separated by at least one week.

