30 minutes after conclusion of the intervention, the MMTT will commence. Blood sampling for subsequent measurements of glucose (NaF plasma tubes), insulin and C-peptide (serum tubes) and incretin and glucagon hormones (EDTA plasma tubes containing aprotinin (500 kiU/mL) and a dipeptidyl peptidase 4 inhibitor (0.01 mmol/L diprotin A) will be performed at the following time points: -30, 0, 30, 60, 90 (start of MMTT), 105, 120, 135, 150, 180, 210, 240 and 270 min. Blood samples for plasma collection will immediately be placed on ice and subsequently centrifuged (2000 g, 15 minutes, 4°C). Samples for serum collection will be left at room temperature for 30 min and centrifuged. Samples will be stored at -80°C until analysis. Plasma glucose will be determined by an enzymatic colorimetric assay (P-Modular, Roche, Switzerland), serum insulin and c-peptide will be measured by electrochemiluminescence immunoassay (E-Modular, Roche, Switzerland) and incretins and glucagon will be measured by radioimmunoassay assays.

RISKS, ADVERSE EFFECTS AND DISCOMFORT

*VO2-max test:* A physical fitness test, where subjects must put in maximum effort. This will cause some degree of breathlessness. VO2max test is a standard method used for scientific purposes in our laboratory.
*DXA scan:* Is not expected to cause significant discomfort. The radiation acquired is so small that it doesn’t cause any risk to subjects. DXA-scan is a standard method used for scientific purposes in our laboratory.

*Pausation of non-insulin anti-diabetic medication:* In order to evaluate the effect of the interventions, it is necessary for subjects to pause medication the days prior to and on the intervention days. It is considered to be without any risk to pause these drugs for shorter time periods.
*Blood sampling:* Will cause minor discomfort in terms of a venous catheter. There is theoretically a risk for infections introduced through the catheter. The blood volume collected is so small that it will cause no symptoms. Blood sampling is a standard method used for scientific purposes in our laboratory.

SUBJECT’S PHYSICAL AND MENTAL INTEGRITY AND PRIVACY

The study will be reported to “Datatilsynet” through Rigshospitalets joint review.

The “Lov om behandling af personoplysninger” will be respected.

ECONOMICAL SUPPORT

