[name] has initiated the study. Different private foundations will be applied for economical support (see attached budget). If economical support is obtained, the ethical committee will be notified. Centre for Physical Activity Research (CFAS) will cover the costs not covered by external foundations. No commercial institutions have been or will be applied for economical support. None of the scientific participants have any disclosures to declare.

Subjects will be paid a fee of DKK 2,000 for participation in the study. The fee is taxable. The fee covers discomfort, time consumption and travel expenses. The fee is paid by the end of the subject's participation. If the subject is excluded or choose to withdraw from the trial, a fee equal to the part of the study the subject has completed will be paid.

ETHICAL ASPECTS

The project is, as described above, expected to result in limited risks, adverse effects and discomfort to the subjects. The subjects will benefit from the study in terms of a thorough medical examination and in terms of introduction to effective training methods.
For research in general, the study is sound and important, and it will contribute to our knowledge about how to increase public health in a large and growing cohort of people with lifestyle diseases.

STATISTICAL ANALYSES

All data will be tested for normality and homogeneity of variance using Kolmogorov-Smirnov and Levene tests. Variables that diverge from parametric assumptions will be log-transformed prior to analysis. Variables of interest will be compared via one-way repeated-measure analysis of variance (RM-ANOVA), and where significant interactions arise, Bonferroni post hoc tests will be applied to identify specific differences between means. Relationships between changes in variables will be examined using regression analyses.

BIOLOGICAL MATERIAL

Blood will be collected in the study. This will be used to assess the potential differential changes in variables following the interventions.

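### The one-way repeated-measures ANOVA has no period term and gives the pre-intervention samples no stated role, so visit drift and visit-to-visit variation in starting values stay in the error term

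*Protocol*

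**What the plan says.** Under Study Design, the protocol sets the order and spacing of the visits: "The 3 interventions will be performed in counter-balanced order and separated by at least one week".

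Under Methods (MMTT), blood is drawn at "30, 0, 30, 60, 90 (start of MMTT), 105, 120, 135, 150, 180, 210, 240 and 270 min"; the first of these times carries a minus sign in the protocol. The day schedule starts the intervention at t = 0, so two samples precede each intervention at every visit.

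Under Statistical Analyses, the comparison is fixed as follows: "Variables of interest will be compared via one-way repeated-measure analysis of variance (RM-ANOVA"). No period, sequence or baseline term is named, and the variables of interest are not defined. Changes in variables are mentioned for the regressions, and under Biological Material for the use of the blood, but not for the ANOVA.

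Under Sample Size, the effect is "standardized effect size = 0.95, (21"), with "α was set at 0.017 (0.05 / 3), and 1-β was set at 0.80", leading to the statement that "at least 12 subjects should complete the study". Subjects who do not complete are replaced, and "the total number of subjects included will not exceed 24".

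**The concern.** A one-way repeated-measures ANOVA has one factor, here the intervention, with subject as the repeated unit. Two sources of within-subject variation that the design could remove are then left in the residual.

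- **Visit order.** Counter-balancing keeps a drift across visits 1 to 3 from favouring one intervention. It does not take the drift out of the error; only a period term does that.
- **Starting level at each visit.** If a subject's fasting glucose differs between visits and the post-meal response follows it, that variation is also residual. The samples at -30 and 0 min precede the intervention, so that day's treatment cannot affect them and they are legitimate covariates.

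With 12 completers, a larger residual lowers the chance of detecting exercise against control and widens the interval for IW-3 against IW-1. The protocol names the model, so this is a comment on a stated choice and not on detail left to a later document.

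**Working it through.** **Inputs.** From the protocol: n = 12, effect 0.95, α = 0.05/3 (given as 0.017), target power 0.80, three visits, counter-balanced order. Assumed: two-sided tests; 0.95 is the mean difference divided by the SD of the paired difference (the protocol does not name the standardiser); equal variances and correlations across visits; all six orders used twice; r, the within-subject correlation between visit baseline and outcome; and the size of any drift.

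**1. The protocol's own figure.** The two-sided normal approximation gives n = ((2.387 + 0.842)/0.95)² = 11.55, so 12. A three-level repeated-measures F test with f = 0.95/2 = 0.475 and an assumed correlation of 0.5 also gives 12. The exact paired t-test gives 13 one-sided and 15 two-sided. The stated 12 is therefore reproduced, although the protocol does not say which test was used.

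**2. Planned model.** Error df = (12 − 1)(3 − 1) = 22. The noncentrality for one pairwise contrast is 0.95 × √12 = 3.29. Against the two-sided critical value at 0.05/3 (2.59), power is 75.2%. Post hoc comparisons made as separate paired t-tests on 11 df would have about 68%.

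**3. Add period.** Error df = 22 − 2 = 20. With no true drift, power is 74.5%, a cost of 0.7 points.

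**4. What drift costs if period is left out.** In units where the paired difference has SD 1, the residual variance is 0.5. A linear drift of s per visit adds 12 × 2s² to the error sum of squares, so the error variance is inflated by (22 × 0.5 + 24s²)/(22 × 0.5).

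- s = 0.25 (0.5 SD from visit 1 to visit 3): (11 + 1.5)/11 = 1.136. In simulation, power is about 70% without the period term and about 74% with it.
- s = 0.3: (11 + 2.16)/11 = 1.196. In simulation, power is about 66 to 68% without and about 74 to 75% with.
- s = 0.15: the loss is only about 1 point (73.1% against 74.1%).

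**5. Add period and the visit baseline.** Error df = 22 − 2 − 1 = 19. The variance factor for the contrast is (1 − r²)(1 + 1/(19 − 1)) = 1.056(1 − r²), and the noncentrality is 3.29/√(factor).

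| r | Variance factor | Power at n = 12 | Change from 75.2% |
|---|---|---|---|
| 0 | 1.056 | 71.4% | −3.8 |
| 0.2 | 1.013 | 73.4% | −1.8 |
| 0.3 | 0.961 | 76.0% | +0.8 |
| 0.5 | 0.792 | 84.6% | +9.4 |
| 0.7 | 0.538 | 95.9% | +20.7 |

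Break-even on variance: 1 − r² = 1/1.056, so r ≈ 0.23 (0.22 for baseline without period, where the factor is 1.05(1 − r²)). Break-even on power, which also pays for the lost df, is r ≈ 0.27.

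**6. Simulation check** (fixed subject effects, six orders twice each). Power for planned / with period / with period and baseline:

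- r = 0: 0.76 / 0.75 / 0.72
- r = 0.5: 0.75 / 0.74 / 0.85
- r = 0.7: 0.75 / 0.75 / 0.96
- r = 0.5 with drift 0.3 SD per visit: 0.68 / 0.75 / 0.85

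These agree with the formulas.

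**The case against.** The strongest reply is that the planned analysis is valid. With balanced orders, one-way contrasts are unbiased, so this is a preference about efficiency. That stands as to bias. It does not remove the point, because the protocol fixes a model that leaves out a factor the design itself controls. Balance is also not assured: non-completers are replaced, and no rule is given for keeping the orders balanced.

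A reader might infer that the pre-intervention samples are ignored altogether. The text does not show that. The variables of interest are undefined and could include changes from the pre-intervention value, and the reference to interactions does not fit a one-way model, so a time-course analysis may be intended. What can be said is that no role is stated for these samples in the ANOVA. Change scores would still omit period, and they fix the baseline slope at 1, which can add noise if the true slope is low.

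A reader might also infer that the change is free. It is free in subjects, visits and samples, but not in degrees of freedom: below r of about 0.22 to 0.27 the baseline term loses power.

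Finally, the protocol standardises the preceding day's food, alcohol, caffeine, vigorous activity, the medication pause and fasting. That may hold down visit-to-visit variation in starting values, and nothing in the document supports r of 0.5 or more. This objection stands: the size of the gain cannot be established from the document.

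**Conclusion.** The point holds as a loss of efficiency in a stated model. It does not show bias while orders are balanced, and it does not show that the planned analysis is invalid. The period term is the firmer half: it costs under 1 point of power without drift and recovers about 4 points at an assumed drift of 0.5 SD from visit 1 to visit 3. The baseline term has an uneven payoff: with period, a loss of about 4 points at r = 0, and gains of about 10 points at r = 0.5 and 20 at r = 0.7. All of these figures rest on 0.95 being in units of the paired-difference SD, on two-sided tests with pooled error, and on assumed values of r and drift that the protocol does not supply. The planned power of about 75% should not be read as proof of a sample-size error, since 12 is reproduced by two routes.

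**What to change.** Replace the one-way model under Statistical Analyses, before any data are seen, with one containing subject, intervention and period (1, 2, 3), plus the mean of that visit's -30 and 0 min values as covariate. Either fit subject as a fixed effect or, if subject is random, enter the baseline as a deviation from the subject's own mean. A raw visit baseline with random subjects mixes the between-subject slope with the within-subject slope, and the gains above would not carry over directly. State also whether each outcome is an absolute value or a change.

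The cost is a few lines of text and three error degrees of freedom (22 to 19), with no added samples or visits. If the sponsor has reason to expect a within-subject correlation below about 0.25, the period term alone is the safer choice.

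### Testing all three pairwise contrasts at 0.05/3 is valid but needlessly conservative for three conditions; Shaffer's step-down keeps family error at 5% and recovers about 7 to 10 points of power for IW-3 versus control

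*Protocol*

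**What the plan says.** The STUDY DESIGN section sets a three-period crossover of IW-3, IW-1 and CON: "The 3 interventions will be performed in counter-balanced order and separated by at least one week". The hypothesis, stated just before EXPERIMENTAL DESIGN, is that "the exercise bouts will improve glycemic control compared with CON but that no differential effect of the exercise bouts" will be seen.

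STATISTICAL ANALYSES compares the variables of interest by one-way repeated-measures ANOVA. Where that is significant, "Bonferroni post hoc tests will be applied to identify specific differences between means". The trigger is worded as significant interactions, which a one-way analysis over condition does not have; the workable reading is a significant condition effect. No sphericity correction is mentioned, and the level of the omnibus test is not given.

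The Sample Size paragraph confirms the size of the correction: "To account for multiplicity, α was set at 0.017 (0.05 / 3), and 1-β was set at 0.80". It concludes that "at least 12 subjects should complete the study", from a standardized effect of 0.95 for IW-3 against CON in an earlier study by the same group.

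**The concern.** Bonferroni guards against up to three true nulls being tested at once. With exactly three means, the number of true pairwise nulls is three, one or none; it cannot be two. If all three are true, the family needs protection as a whole. If one is false, at most one true null is left, and a single 5% test controls it. Holding every pairwise test at 0.05/3 ignores this structure.

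What is at stake is power in a trial of 12. The stated aim covers both bouts against control, and that joint claim loses most.

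**Working it through.** **Inputs.** From the protocol: three conditions, 12 completers, per-test level 0.05/3, effect 0.95 for IW-3 versus CON. Assumed, because the protocol does not say: omnibus level 0.05; two-sided tests; 0.95 is on the paired-difference scale; the same effect applies to IW-1; post hoc tests are paired t-tests. The ratio SD(IW-3 − IW-1) / SD(IW − CON) is varied from 1.0 (sphericity) to 0.5.

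**The plan's own figure.** Normal approximation, two-sided: n = ((z₀.₉₉₁₅ + z₀.₈₀)/d)² = ((2.387 + 0.842)/0.95)² = 11.55, so 12. The stated number reproduces. A two-sided paired t-test at 0.017 needs 15 and has 68.2% power at 12. One-sided, it needs 13 and has 79.5% at 12.

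**One contrast, no gate.** Noncentrality = 0.95 × √12 = 3.291 on 11 df.
- At 0.05/3 the critical t is 2.820 and power is 67.8%.
- At 0.05 the critical t is 2.201 and power is 84.9%.

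**Full rules, by simulation** (n = 12, 200,000 trials per setting). Ranges run over SD ratios from 1.0 to 0.5.

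| Rule | Power, IW-3 vs CON | Power, both bouts vs CON | Family error, all three equal | Family error, only two equal |
|---|---|---|---|---|
| As written: ANOVA at 0.05, then 0.05/3 | 67–68% | 52–60% | 2.7–3.2% | 1.6–1.7% |
| Shaffer: smallest p at 0.05/3, then the other two at 0.05 | 75–78% | 72–73% | 4.1–4.5% | at most 5% |
| Greenhouse-Geisser ANOVA at 0.05, then 0.05 | 81–84% | 75–80% | 4.2–4.9% | at most 5% |
| Uncorrected ANOVA at 0.05, then 0.05 | 82–85% | 75–80% | 5.0–6.2% | at most 5% |

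Differences taken before rounding, against the written rule:
- Shaffer gains about 7 to 10 points for IW-3 versus CON and about 13 to 19 for both bouts.
- The corrected gate gains about 14 to 16 and 20 to 23 points.

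**Why Shaffer is never worse.** Any rejection under the written rule has p below 0.05/3. The smallest p is then also below 0.05/3, so Shaffer opens its second step and rejects the same contrast. When all three are equal, Shaffer errs only if the smallest p is below 0.05/3, exactly as ungated Bonferroni does.

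**Sensitivity.**
- With the pooled ANOVA error term under sphericity, the gated rule goes from 75% to 85%, about 10 points.
- At n = 15 the written rule has about 81% and the corrected gate about 91%, again about 10 points.
- If IW-1's effect were 0.5 (assumed), Shaffer's gain for IW-3 versus CON falls to about 5 points (70.9 − 66.4 at ratio 1.0; 72.7 − 67.7 at 0.7). The corrected gate's gain falls to about 10.

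**The case against.** The written rule is valid with paired tests, is standard, and agrees with the level used for sizing. Nothing is contradicted and no error is inflated. That stands: this is lost efficiency, not a flaw in error control. It does not defeat a replacement that rejects at least as much at the same 5% family level.

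A reader might infer something stronger: that the ANOVA gate already holds family error at 5%, so Bonferroni corrects twice and protects against nothing. The protocol does not support this, for three reasons.
- The gate has no sphericity correction. Used alone with 0.05 tests it gives 5.0% to about 6.2% when the two bouts resemble each other more than control, so Bonferroni does protect against something.
- The low power does not come from pairing the gate with Bonferroni. Bonferroni with no gate gives 67.8% and adding the gate gives 67.3%. The loss comes from fixing every test at 0.05/3.
- The argument covers one value per condition. The word interactions, together with the 13 sampling times in METHODS, leaves room for a condition-by-time analysis with comparisons at time points. There the three-means logic would not protect.

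A reader might also suppose that adjusted p-values will be compared with 0.017, a further correction. Nothing says so; 0.017 appears only as a planning level.

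Finally, the power figures depend on sidedness, on the scale of the 0.95 and on IW-1's effect, none of which the protocol gives.

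**Conclusion.** The concern holds as a point of efficiency. For a single summary value per condition, testing every contrast at 0.05/3 uses about 1.6 to 3.2% of a 5% family error. Under the stated assumptions it leaves about 67 to 68% power for IW-3 versus control and 52 to 60% for both bouts. Shaffer's step-down recovers about 7 to 10 points on the first with no added assumption. The Greenhouse-Geisser gate recovers about 14 to 16. Gains are smaller with pooled-error tests, at n = 15, or if IW-1 has a weaker effect. It would be wrong to say that the gate as written makes Bonferroni redundant, or that the planned analysis inflates error.

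**What to change.** In STATISTICAL ANALYSES, replace the Bonferroni sentence with, for example:

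*For each variable, one summary value per condition is compared between IW-3, IW-1 and CON by two-sided paired t-tests. Family error is held at 0.05 by Shaffer's step-down: the smallest p-value is tested at 0.05/3 and, if it is significant, the other two are each tested at 0.05. The repeated-measures ANOVA condition effect is reported but does not gate these tests.*

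Alternatively, keep the gate: omnibus test of the condition effect at 0.05 with Greenhouse-Geisser correction and, if significant, each pairwise test at 0.05. The sphericity correction is then required.

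Either way, change interactions to condition effect, and state that the rule does not cover comparisons at individual time points.

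Leave the planning level in the Sample Size paragraph as it is unless power is recomputed for the full procedure. Resetting it to 0.05 would ignore the first step's own power and allow a smaller trial: a two-sided paired t-test would then need only 11, where the gated rule has about 77%.

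Cost: a few sentences; no subjects, visits or assays. Unadjusted pairwise intervals lose simultaneous coverage and must be labelled so. IW-3 versus IW-1, expected to be null, would be wrongly rejected more often than the present 1.6 to 1.7%, but still within 5%.
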